### Ethical Considerations

The MINA-Brazil birth cohort was approved by the Ethics Committee in Research with Human Beings of the School of Public Health of the University of São Paulo (protocols 872,613 of November 13, 2014, and 872,613 of October 30, 2017). For this trial, a new protocol was submitted and approved by the same Ethics Committee in Research with Human Beings (protocol 5,805,325 of December 9, 2022). Before taking part in the study, consent forms will be collected from parents or caregivers, and assent forms will be collected from children to guarantee the voluntary nature of participation. Additionally, participants will be informed of the minimal anticipated harms of the intervention, such as the possibility of discomfort related to interviews with personal questions and venous blood collection, which will involve trained professionals and disposable materials. All participants will receive appropriate information on what to do if they wish to withdraw from the intervention at any time.

### Baseline Information and Randomization

Face-to-face individual data collection meetings will take place before the beginning of the intervention to explain the study to parents or caregivers and schedule fasting blood collection at a local laboratory. After recruitment and data collection, participants will be randomly assigned to each experimental group using the R software (R Foundation for Statistical Computing), according to children’s sex, age, and BMIz quartile intervals. Additionally, the stratified sortition will consider parents’ or caregivers’ schooling in years (≤9, 10-12, or ≥13) and wealth index quartiles.

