### Overview and Trial Design

This trial will be a parallel randomized controlled trial nested in MINA-Brazil, the first population-based birth cohort based in Cruzeiro do Sul, Acre State, in the Western Brazilian Amazon. The cohort was designed to investigate the determinants of maternal and child health and have as participants children born at the Hospital Estadual da Mulher e da Criança do Jurua, in Cruzeiro do Sul, in the period between July 2015 and June 2016. Participants have been followed up for 5 years, and the last evaluation of health status took place in 2021. This protocol was prospectively registered in the Brazilian Clinical Trials Registry (RBR-5zdnw6t; date of registration: March 30, 2023; UTN code: U1111-1289-0560) and has been described according to the CONSORT-EHEALTH checklist (version 1.6.1; Multimedia Appendix 1 [37-47]) [48]. Table 1 shows the timeline of the study activities according to the intervention stage:

**Table 1 table1:** Timeline of the study activities according to intervention stages.

Stage of intervention	Recruitment	Baseline	Intervention period	Postintervention
Verbal consent for screening	✓			
Eligibility screening verification	✓			
Study invitation	✓			
Face-to-face individual interview		✓		
Written consent from parents and written assent from children		✓		
Sociodemographic and participant information collection		✓		
Anthropometric measures		✓		✓
Food frequency questionnaire administration		✓		✓
Biochemical data collection		✓		✓
Strengths and Difficulties Questionnaire administration		✓		✓
Short version of the Brazilian Food Insecurity Scale administration		✓		✓
Delivery of an educational booklet		✓		
Goals setting for intervention group			✓	
Multimedia messaging for a 19-week follow-up			✓	
Phone call at 1 week to check if caregivers are properly receiving the messages			✓	
Goal achievement assessment for intervention group				✓
Delivery of same intervention to waitlist control group.				✓

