**Figure 1 figure1:**
[figure not shown]
Study flowchart. BMIz: BMI in *z* score; MINA-Brazil: Maternal and Child Health and Nutrition Cohort Study in Acre; MMS: Multimedia Message Service.

Inclusion criteria for the study include (1) being a guardian of a child aged between 7 and 8 years enrolled in MINA-Brazil, (2) owning a cell phone that can install the WhatsApp app, (3) having internet access at least once a week, and (4) being literate and having internet literacy.

Exclusion criteria include (1) dietary restrictions or special diets that limit a child’s ability to eat a variety of foods (eg, children on treatment for any disease that requires a specific diet), (2) simultaneous participation in another nutritional or weight loss program, and (3) not having the availability to follow up on the intervention for the whole period between baseline and final data collection (eg, intending to move out of town).

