### Power and Sample Size Calculation

The sample size estimation used the expected effect size (E) of at least 10% change for the mean value of BMIz as the main outcome (*z* score=1.5) and SD of 3.5 in a 2-tailed distribution, considering a *P* value of .05, statistical power of 80% (β=20%), and sample size ratio (group 1/group 2) of 1:1. Thus, for the expected E/SD ratio, the minimum sample required must be 100 participants per group [49]. However, assuming a dropout rate and potential losses of 20% during the intervention period, the sample size to be enrolled at baseline will be at least 120 children per study group [49].

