## Results

Data collection started in June 2023, and 266 children were enrolled at baseline. Final measurements are scheduled to be completed in December 2023. The results of the main analysis will be conducted in 2024 and are expected to be available in 2024 and 2025.

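### Five stratification factors, if fully crossed, give at least 96 sparse cells for 266 children; this weakens but does not remove balance, and the unadjusted tests ignore the factors and baseline BMIz

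*Protocol article*

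**What the plan says.** Protocol article, Baseline Information and Randomization: "After recruitment and data collection, participants will be randomly assigned to each experimental group using the R software", "according to children’s sex, age, and BMIz quartile intervals". The next sentence adds that "the stratified sortition will consider parents’ or caregivers’ schooling in years"; in full, the added factors are "schooling in years (≤9, 10-12, or ≥13) and wealth index quartiles". The section does not state how many age levels there are, how children are split within a stratum, or whether all factors are crossed.

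Other facts that bear on the point:
- Power and Sample Size Calculation gives a "sample size ratio (group 1/group 2) of 1:1" and a target of at least 120 children per group.
- Results reports that "266 children were enrolled at baseline".
- The cohort was born "in the period between July 2015 and June 2016" (Overview and Trial Design), and eligibility requires "being a guardian of a child aged between 7 and 8 years" (Study Population and Setting).
- Data Analysis names paired and unpaired t tests of mean changes, the Mann-Whitney test for skewed data, and multiple imputation. It names no adjustment for the randomisation factors or for baseline BMIz.

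**The concern.** Stratification balances a factor well only when most strata hold several children. Each stratum with an odd count leaves one child to chance, and a child alone in a stratum is in effect randomised without restriction. As factors are added, these leftovers accumulate and control over each single factor weakens.

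The factor that matters most here is baseline BMIz, because the primary outcome is the change in BMIz. Age adds cells but little information: the children were born within 12 months of each other, and BMIz is already standardised for age and sex. At stake is some avoidable chance imbalance in baseline BMIz and arm size, together with an analysis that does not use the factors to recover precision.

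**Working it through.** The article gives no number of strata and no balance figure, so there is nothing of its own to reproduce.

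**Cells.** Sex 2, BMIz quartile 4, schooling 3, wealth quartile 4: 2 x 4 x 3 x 4 = 96. Age levels are not stated. Two levels give 96 x 2 = 192, and four give 96 x 4 = 384.

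**Children per cell.** 266/96 = 2.77; 266/192 = 1.39; 266/384 = 0.69.

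**Balance.** Simulation of 266 children (4,000 runs) with factors crossed and independent, schooling in thirds, and BMIz in SD units. Each cell is split evenly, with any odd child placed at random. Simple randomisation of the same children is the reference.

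| Scheme | Single-child cells | Odd cells | SD of arm-size difference | 95th pct. arm-size difference | SD of baseline BMIz difference | 95th pct. BMIz difference |
|---|---|---|---|---|---|---|
| 96 cells | 16 | 48 | 6.9 | 14 | 0.067 | 0.13 |
| 192 cells | 67 | 91 | 9.8 | 20 | 0.081 | 0.16 |
| 384 cells | 135 | 146 | 12.1 | 24 | 0.095 | 0.18 |
| Simple randomisation | – | – | about 16.3 | 32 | 0.122 | 0.24 |
| BMIz quartile only | – | – | 1.4 | 2 | 0.047 | 0.09 |

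Sex x BMIz quartile (8 cells), run with blocks of 4, gives 95th percentiles of 4 children and 0.10 SD.

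**Hand check of arm size.** Each odd cell contributes +1 or -1, so the SD is about the square root of the number of odd cells: √48 = 6.9, √91 = 9.5, √146 = 12.1. Simple randomisation gives √266 = 16.3. Multiplying by 1.96 gives 13.6, 18.7, 23.7 and 32.0. With 8 cells about half are odd, so 1.96 x √4 = 3.9. These agree with the simulation.

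**Share of imbalance variance removed, relative to simple randomisation.** For 96, 192 and 384 cells the variance ratios are 0.18, 0.36 and 0.56 for arm size, and 0.30, 0.45 and 0.59 for BMIz. So 82%, 64% and 44% of the arm-size variance is removed, and 70%, 55% and 41% of the BMIz variance. Against BMIz quartile alone, the BMIz imbalance variance is (0.067/0.047)² = 2.0 to (0.095/0.047)² = 4.1 times larger.

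**Sensitivity.** With correlated factors and a 30/45/25 schooling split, the 95th percentiles of the BMIz difference are 0.13, 0.15 and 0.18. With 240 children they are 0.14 (96 cells) and 0.17 (192 cells). With blocks of 4 instead of an even split they are 0.15, 0.19 and 0.22.

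**Cost of unequal arms.** A difference of 24 is 121:145. Efficiency relative to 1:1 is 4 x 121 x 145 / 266² = 70,180/70,756 = 99.2%.

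**Effect on a change-score test.** With equal SDs and pre-post correlation ρ, a baseline difference d shifts the expected difference in change by (1 - ρ)d in the opposite direction. The article gives no ρ. Assuming 0.8 to 0.9, d = 0.13 to 0.18 leaves between 0.1 x 0.13 = 0.013 and 0.2 x 0.18 = 0.036 SD.

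**Gain from adjusting for baseline.** The variance of the effect estimate under ANCOVA relative to the change score is (1 - ρ²)/[2(1 - ρ)] = (1 + ρ)/2: 0.90 at ρ = 0.8 and 0.95 at ρ = 0.9. That is a 5% to 10% reduction, before any gain from the other factors.

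**The case against.** A reader might infer that the stratification largely fails and that the trial is close to simple randomisation. The document does not support this, for four reasons.

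- **Crossing and blocks are not stated.** Saying that schooling and wealth are considered could also describe balancing on the margins, which avoids sparse cells. No blocks are mentioned. Because allocation follows baseline data collection, stratum sizes are known and blocks left unfilled by sequential entry need not arise. An article may leave such detail to the full protocol.
- **Balance is still clearly better than under simple randomisation.** At 96 cells an even split removes most of the imbalance variance. Only 384 cells with incomplete blocks of 4 comes near failure (variance ratios 0.83 for arm size and 0.78 for BMIz).
- **The harm is small.** Randomisation stays unbiased, unequal arms cost under 1% of efficiency, and analysing change removes most of a chance baseline difference when pre-post correlation is high.
- **Allocation has probably been run,** since enrolment is reported as complete at 266.

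All of this stands, and it limits the point to weakened balance. It does not remove the point. Full crossing is the ordinary meaning of a stratified draw, 96 is a floor because age is a named factor, and a shorter list would control baseline BMIz better. The change score also leaves part of any imbalance in place and does not use the other factors.

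**Conclusion.** The point holds in a limited form. If the five factors are fully crossed, there are 96 to 384 cells for 266 children. With an even split, the 95th percentile of the baseline BMIz difference is then about 0.13 to 0.18 SD, which lies between the short list (about 0.10) and simple randomisation (about 0.24). Arm sizes differ by up to about 14 to 24 children, against 4 and about 32. This is a loss of efficiency in the design. It is not a threat to validity, and it does not mean that stratification fails.

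The part that can still be acted on is the analysis: the tests named in Data Analysis leave the randomisation factors and baseline BMIz unused. The figures assume full crossing, age in one, two or four levels, a schooling split the article does not give, and an even split within cells. Blocks of 4 would make balance somewhat worse. The size of the residual effect and of the ANCOVA gain rests on the assumed ρ of 0.8 to 0.9.

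**What to change.** **If allocation has been run:** keep it, and state the age levels and the within-stratum method that were used. Replace the unadjusted between-group test of BMIz change with a linear model (ANCOVA) that contains arm, baseline BMIz and the stratification factors as main effects. With baseline BMIz and age as continuous terms, this takes 1 + 1 + 1 + 2 + 3 = 8 parameters (BMIz, age, sex, schooling, wealth). Do not use cell indicators: 96 cells need up to 95 parameters, and children alone in a cell contribute nothing to the comparison (about 67 of 266, or 25%, at 192 cells). The unadjusted test can remain as a sensitivity analysis. The cost is model wording, settled before the data are compared by arm.

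**If allocation has not been run:** drop age as a factor, and balance the margins of BMIz quartile, sex, schooling and wealth by minimisation with a random element or by constrained randomisation. This is possible because all baseline data precede the single draw in R. The cost is a different R routine and documentation of its random element. The same ANCOVA then applies.

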### Blinding

Given the nature of the intervention, we cannot guarantee participants will be blinded. However, study participants will not be aware of which group they will be assigned to. All participants will be informed that they will take part in a nutritional program; however, some children will receive the intervention before others. Furthermore, this strategy aims to minimize the chances of contamination bias due to information exchange between participants in the control and intervention groups. Researchers will be aware of participants’ allocation, but all analyses will be blind to allocation.

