### Control Group

The control group will consist of children from the same population as the intervention group to ensure that both groups share similar characteristics, thereby guaranteeing accurate results for the intervention. In this context, the control group will not receive any messages during the intervention period. However, participants allocated to this group will be informed that they are on a waiting list and that the intervention will be carried out in stages, where children will receive the intervention at different times. After the end of the intervention period, the control group will receive the same treatment as the intervention group [35].

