### Primary Outcome (BMIz)

Children in both experimental groups will have their weight and height measured by trained study researchers according to the parameters established by the WHO [62]. BMIz and children’s anthropometric indices, weight for age and height for age, will be assessed through WHO Anthro-Plus software and will be interpreted as recommended by the WHO [63]. In addition, children’s waist circumference (WC) will be measured according to WHO recommendations [64]. Since no WC cutoff points were found in the literature for Brazilian children, to evaluate WC, we will consider that children with WC values above the 90th percentile of the sample have excessive abdominal fat [65,66]. The waist-to-height ratio will also be calculated, in which values above 0.5 will be considered to correspond to the presence of excessive abdominal fat [65,67].

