### Secondary Outcomes

#### Dietary Habits

In natural and minimally processed food (fruits, vegetables, grains, tubercles, and cereals) and UPF (chocolate powder, artificial and soft drinks, industrial bread, sweet-filled biscuits, salty crackers, deli products, pre-prepared frozen foods, instant noodles, sweets, and candies, among others), consumption will be assessed through a 1-month validated food frequency questionnaire for Amazonian schoolchildren [68]. Data will be collected by a trained nutritionist, and the frequency of food consumption will comprise the following 8 categories: rarely, 1-3 times a month, 1-3 times a week, 1 time a day, 2-3 times a day, 4-6 times a day, and more than 6 times a day.

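### Post-intervention weight and height, the inputs to BMIz, may be recorded by staff who know the arm, and the statement on participant awareness conflicts with the rest of the plan

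*Protocol article*

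**What the plan says.** **Researchers and assessors.** The Blinding section says: "Researchers will be aware of participants’ allocation, but all analyses will be blind to allocation". It makes no exception for people who collect outcomes. Under Primary Outcome (BMIz), the plan says: "Children in both experimental groups will have their weight and height measured by trained study researchers". For waist it says only that "children’s waist circumference (WC) will be measured according to WHO recommendations", without naming who measures. For the food frequency questionnaire, the Dietary Habits section says: "Data will be collected by a trained nutritionist". It does not say whether that person knows the arm.

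**Participants.** The Blinding section opens by saying that participant blinding cannot be guaranteed. It then says that "study participants will not be aware of which group they will be assigned to". The Control Group section says that "participants allocated to this group will be informed that they are on a waiting list" and that controls get no messages during the intervention period. The Intervention Plan gives the other arm messages three times a week for 19 weeks, two chosen goals and a phone call at one week.

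**Timing.** Under Baseline Information and Randomization, assignment follows recruitment and data collection. In Table 1 (Overview and Trial Design), the postintervention column contains anthropometry, the questionnaires and blood collection. It also contains "Goal achievement assessment for intervention group" and delivery of the intervention to the waitlist group.

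**The concern.** Two separate problems follow, and they fall on different outcomes.

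1. **Assessor knowledge.** If the person who positions the child and reads the stadiometer knows the arm, a small systematic difference in reading can enter the follow-up value. Because baseline was taken before randomization, such an error at one time point passes in full into the between-arm difference in change. A blinded analyst receives the values as recorded and cannot correct them. At stake is the credibility of the primary comparison, in which the expected effect is small.

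2. **Participant knowledge.** By follow-up each family can work out its arm. The food frequency questionnaire asks about fresh and ultraprocessed foods, which are also the subject of the first two message topics. Answers may shift towards what the messages recommend whether or not the diet has changed. The same openness applies to the Strengths and Difficulties Questionnaire (SDQ), which caregivers complete, and to the food insecurity scale. A sentence saying that participants do not know their group gives the wrong picture of these data.

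**Working it through.** The plan gives no figure on this point, so the main check sets the sections side by side.

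**Step 1: who may know the arm at follow-up**

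| Measurement | Who records it | Knowledge of arm in the plan |
|---|---|---|
| Weight, height (BMIz) | Trained study researchers | Researchers know the allocation, with no exception given |
| Waist | Not named | Not stated, no masking described |
| Food frequency questionnaire | Trained nutritionist | Not stated, no masking described |
| SDQ | Parent or caregiver | The family can infer its arm |
| Food insecurity scale | Not named | The family can infer its arm |
| Lipids, glucose, insulin | Local laboratory, automated | Little room for assessor or reporting bias |

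Only weight and height are linked to allocation-aware staff by the plan's own words. For waist and diet, the most that can be said is that no masking is described.

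**Step 2: which visit is exposed.** Baseline data collection precedes assignment, so only the post-intervention visit is exposed.

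**Step 3: participant awareness.** The plan makes four statements: blinding cannot be guaranteed; participants will not be aware of their group; controls are told that they are on a waiting list; one arm gets messages three times a week and the other none. The second cannot hold alongside the third and fourth once the intervention has started, and it sits badly with the first.

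**Step 4: scale of an assessor error (illustration only).** Assumed inputs, not in the plan: height H = 125 cm, BMI 16 kg/m², BMI SD 1.5 to 2.0 kg/m², and a systematic difference h = 0.5 cm between the arms.

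- BMI shift = BMI × [1 − (H/(H + h))²] = 16 × [1 − (125/125.5)²] = 0.127 kg/m².
- In SD units: 0.127/2.0 = 0.064 and 0.127/1.5 = 0.085, so about 0.06 to 0.09 BMIz.
- For comparison, if the target in Power and Sample Size Calculation is read as 10% of 1.5, it is 0.15 BMIz. The shift is then 0.064/0.15 = 43% to 0.085/0.15 = 57% of it.

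**Step 5: effect on the test.** With n = 100 per arm, SE = SD × √(2/100). With no true effect and a bias b, the two-sided false-positive rate is Φ(b/SE − 1.96) + Φ(−b/SE − 1.96). The values b = 0.05 and 0.10 bracket the shift in step 4.

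| SD of change | b = 0.05 | b = 0.10 |
|---|---|---|
| 0.4 (assumed) | 14.3% | 42.4% |
| 0.5 (assumed) | 10.9% | 29.3% |
| 1.0 (assumed) | 6.4% | 10.9% |
| 3.5 (the SD in the sample size section) | 5.1% | 5.5% |

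The consequence ranges from negligible to serious according to an SD of change that is not known. The size of diet reporting bias cannot be derived from the document.

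**The case against.** Several points on the other side are sound.

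- **Weight and height are objective**, taken by trained staff to WHO parameters. The illustration needs a mean shift across a whole arm, not ordinary reading error, and nothing in the plan suggests that a 0.5 cm shift will occur. This stands: the figures show what such an error would do, not that it is likely.
- **The researchers who know the allocation need not be the people who measure.** The plan uses the same word for both and makes no exception, so the reading is fair, but it supports only that the measurers may know the arm.
- **The plan does not promise participant blinding.** It says at the outset that it cannot be guaranteed, and the awareness sentence could refer to the time before assignment. This softens the conflict. The sentence still carries no such limit and stands in the Blinding section.
- **The order of tasks within a visit is field-manual detail** that an article may leave out. Table 1 lists measurements above goal assessment and waitlist delivery, without saying that the rows are chronological. The missing order is therefore not an error in itself.

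A reader might go further and infer that the waist assessor and the nutritionist know the arm, or that every non-laboratory outcome is open to both assessor and reporting bias. The document does not support either. Knowledge of the arm is not stated for those two roles, and what families report cannot change a measured height, weight or waist.

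**Conclusion.** The point holds in limited form. By the plan's own words, post-intervention weight and height, and so BMIz, may be recorded by people who know the arm, and blind analysis does not protect against that. Baseline is unaffected. For waist and the diet interview, masking is simply not described. Separately, the participant-awareness sentence is inconsistent with other parts of the plan, and the diet, SDQ and food insecurity data should be regarded as unblinded reports.

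The possible size in BMIz, about 0.06 to 0.09, rests wholly on the assumed body size, BMI SD and 0.5 cm systematic difference, and its effect on the test rests on the unknown SD of change. This is a worthwhile improvement to the conduct and description of the trial. It does not show that the primary result will be biased, and it does not invalidate the design.

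**What to change.** **At the post-intervention visit:**

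1. Take weight, height and waist and complete the diet questionnaire first, on a CSPro form that shows only the participant ID.
2. Limit allocation access to existing staff who do not measure or interview. Messages go out through a programmed system, so few people need the list.
3. Ask families not to mention messages until these steps are done.
4. Only then do the goal assessment and the waitlist delivery.

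**In the text:**

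- State in the Blinding section whether the staff who record post-intervention anthropometry and diet are kept unaware of the arm.
- Replace the participant-awareness sentence with a statement that families can infer their arm once the intervention starts.
- Report dietary outcomes as unblinded reports.

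The article describes final measurements as still to come, scheduled to finish in December 2023. If they have already been taken, the remedy is to report who knew the allocation when each outcome was recorded and to make the text corrections.

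**Cost:** some separation of roles among existing staff, one hidden field in the form and some visit logistics. No extra assessors are needed.
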